## Abstract

**Background and Study Design:**

Role of ^18^F‐fluoro‐2‐deoxy‐2‐d‐glucose positron emission tomography‐computed tomography (FDG PET‐CT) in evaluation of renal cell cancers (RCC) and urinary bladder cancers is not standardized, and the COPPER‐T trial, which is a single centre prospective randomized study, was designed to compare it with conventional imaging for staging of clinically localized high risk RCC and urinary bladder carcinoma (Stage T2 and above).

**Patients and Methods:**

There will be two subgroups of patients: RCC and urinary bladder carcinoma. In each of these, the patients will be randomized to either Arm A or Arm B. In each of the arms, each patient will be subjected to diagnostic imaging by FDG PET‐CT. The CT scan will be a contrast‐enhanced scan like that in conventional staging. A radiologist and nuclear medicine specialist will report the scan independently. The radiologist will not have access to the PET scan sequences and will only review the contrast‐enhanced computed tomography (CECT) images. In Arm A, the report of the conventional imaging modality, that is, CECT and bone scan if done, will be reviewed first by the clinician, and based on this report, a management plan will be made. Then, the PET‐CT report will be reviewed, and change in the management plan will be noted. New findings or equivocal findings if any in the PET‐CT report would be noted. In Arm B, the report of the PET‐CT report will be reviewed first by the clinicians, and a management plan will be made. Then, the CECT and/or bone scan reports will be reviewed, and any change in the management plan will be noted.

**Outcome and Significance:**

Final analysis of the data after completion of the trial will help in clarifying the role of FDG PET‐CT in high risk RCC and transitional cell carcinoma (TCC) of the bladder, its diagnostic accuracy compared with conventional imaging and the impact of using it on patient management.

## INTRODUCTION

1

One third of all cases of renal cell carcinoma (RCC) have synchronous metastases at presentation.^1^ An additional 20–40% of patients with clinically localized disease at presentation will eventually progress and develop metastases.^2^ Metastatic RCC is almost always fatal with 5‐year survival rates of less than 15%.^3^ Therefore, accurate staging of newly diagnosed RCC is of paramount importance. Transitional cell carcinoma of the urinary bladder is the 12th most common malignancy.^4^ About 5–10% of all cases are metastatic at presentation.^5^ Almost 25–30% of all urinary bladder malignancies present with muscle invasive disease,^5^ and even with multidisciplinary decision‐making, there is a significant risk of under staging. Of the patients who undergo curative surgical resection, a significant proportion of patients ultimately experience disease relapse and progression with poor outcomes. This progression can be attributed to systemic disease at presentation which has escaped detection by conventional and recommended imaging modalities.

At present, both the National Comprehensive Cancer Network and European Association of Urology guidelines recommend contrast‐enhanced computed tomography (CECT) of the chest and abdomen for the initial staging of high risk RCC and urinary bladder cancer.^6^, ^7^, ^8^, ^9^ Bone scan is recommended only when there are symptoms suggestive of bony involvement or elevated alkaline phosphatase levels. Although ^18^F‐fluoro‐2‐deoxy‐2‐d‐glucose positron emission tomography (FDG PET) scan is an integral part of the staging and evaluation of many other cancers, its exact role in the evaluation and management of newly diagnosed RCC and urinary bladder cancer remains to be elucidated.^10^, ^11^ At present, both the National Comprehensive Cancer Network and European Association of Urology do not recommend the use of FDG PET as an initial staging modality in RCC and bladder cancer. Newer tracers, including those targeting fibroblast activation protein, are under evaluation in imaging of multiple cancers, including renal and urinary bladder cancers, and may prove to have higher sensitivity than FDG, but that is yet to be elucidated.^12^, ^13^ Nevertheless, there is a large body of literature in recent times that point towards the increased sensitivity of FDG PET‐CT in detecting distant metastases, compared with conventional imaging, in the initial staging of RCC and carcinoma urinary bladder, although this has not been proven in a head‐to‐head randomized controlled trial.^11^

## COPPER‐T—CLINICAL TRIAL OVERVIEW

2

COPPER‐T, that is, COmParison of FDG PET‐CT with conventional imaging in the staging of high‐risk Renal cancers and Transitional cell carcinoma of bladder, is a single centre prospective randomized controlled trial that compares FDG PET‐CT to conventional imaging (CECT scan of the abdomen and bone scan wherever appropriate) for staging of clinically localized high risk RCC (>Stage T2) and urinary bladder malignancy (>Stage T2 and higher). The goal of this trial is to provide robust high‐level data on whether FDG PET‐CT should replace conventional imaging in the assessment of such patients or whether it should be used only in providing incremental diagnostic information in select cases. The hypotheses of this study are (a) FDG PET‐CT has improved diagnostic accuracy compared with conventional imaging modalities, (b) FDG PET‐CT should be used as the first line imaging modality in high risk RCC and bladder cancer and (c) the improved diagnostic accuracy of FDG PET‐CT will result in significant management impact in these patients. The primary objective of this study is to compare diagnostic accuracy of FDG PET‐CT to that of conventional imaging for detecting distant and nodal metastases in these patients. The secondary objectives have been listed below:
To compare the first line management impact of FDG PET‐CT to conventional imaging.To compare the number of equivocal study results between the two modalities.To assess the incremental accuracy of FDG PET‐CT or conventional imaging as a second line imaging modality by their ability to detect additional metastases over the first lime imaging performed.To determine the impact of FDG PET‐CT or conventional imaging as a second line imaging modality over the first line imaging on the management of patients.

The tertiary objectives are the following:
To evaluate the prognostic value of FDG PET‐CT with regard to the disease‐free status (3 years from accrual of the last patient).To report the acute adverse events for FDG PET‐CT if any.To evaluate the utility of SUVmax in predicting histopathology and grade of RCC in the subset of patients with RCC.

## PATIENTS AND METHODS

3

We aim to evaluate the role of FDG PET‐CT in patients of RCC and urinary bladder carcinoma with a significant risk of metastatic disease. Patients of RCC and urinary bladder carcinoma will be kept in different subgroups and will undergo separate analysis and follow‐up. The inclusion and exclusion criteria have been outlined below.

Inclusion criteria are as follows:
All patients attending the urology OPD of AIIMS, Jodhpur, and more than 18 years of age with imaging or biopsy findings suggestive of primary renal malignancy TNM Stage T2 and/or N1 and above.All patients attending the urology OPD of AIIMS, Jodhpur, and more than 18 years of age with imaging or biopsy findings suggestive of muscle invasive carcinoma urinary bladder or N1 and above.All patients giving written informed consent.All patients willing and able to comply with the required procedures of the study in the opinion of the investigator.

Exclusion criteria are as follows:
Any patient not giving consent for the study.Any patient with poor performance status or life expectancy excluding him/her from curative surgery or radiotherapy or use of oral/intravenous therapy.Known case of renal, upper tract urothelial cancer (UTUC) or bladder malignancy post curative intent.Known case of metastatic malignancy already on treatment for advanced disease.Patient with compromised renal function in whom administration of intravenous (IV) iodinated contrast is contraindicated.Patient with known hypersensitivity to the radiotracer or contrast agent to be used.A history of other known malignancy within the last 2 years with the exception of melanoma or any other known skin cancer.

The study is approved by the All India Institute of Medical Sciences, Jodhpur Ethics Committee and is prospectively registered in the Clinical Trials Registry of India and WHO ICTRP bearing trial no. CTRI/2022/07/043691.

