### Clinical management

4.3

Clinical management of patients within this study is at the discretion of two individual clinicians working within a multidisciplinary framework. The study protocol does not determine how patients are managed; however, the management impact of each imaging modality is recorded by the treating clinician after reviewing the reports of each scan. As these patients are being considered for localized treatment at the time of inclusion, it is expected that the majority of patients within the study will proceed to radical surgery. Pathological findings at surgery will be compared with imaging.

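### The stated population is clinically localized disease, but the entry criteria admit suspected nodal disease and do not exclude untreated metastatic disease; separately, they exempt recent melanoma

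*Protocol article*

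**What the plan says.** **Stated population (protocol article).** The abstract gives the purpose as "staging of clinically localized high risk RCC and urinary bladder carcinoma (Stage T2 and above"). Section 2 (overview) has "staging of clinically localized high risk RCC (>Stage T2) and urinary bladder malignancy (>Stage T2 and higher"). Section 4.3 (Clinical management) adds: "As these patients are being considered for localized treatment at the time of inclusion".

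**Entry criteria (section 3, Patients and methods).**
- RCC: "imaging or biopsy findings suggestive of primary renal malignancy TNM Stage T2 and/or N1 and above".
- Bladder: "imaging or biopsy findings suggestive of muscle invasive carcinoma urinary bladder or N1 and above".
- The only exclusion that concerns metastatic disease: "Known case of metastatic malignancy already on treatment for advanced disease".
- Other cancers: "A history of other known malignancy within the last 2 years with the exception of melanoma or any other known skin cancer".

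**Target condition and positivity.** Section 2 makes the detection of nodal and distant metastases the primary objective. Under section 4.1 a scan is positive if any one of three criteria is met, and a typical look on the scan is one of them. Confirmation by biopsy or other imaging is encouraged but left to the clinicians.

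**The concern.** The population named in the objective and the population that can be enrolled are not the same. Nodal disease suspected on earlier imaging is a route into the trial, and because of the words and/or (RCC) and or (bladder) it qualifies even without the T criterion. A newly found, untreated metastatic patient meets the inclusion criteria and is caught by no exclusion. The fitness exclusion concerns performance status and life expectancy, not stage.

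The trial asks whether PET-CT finds nodal and distant disease that conventional imaging misses in patients thought to be localized. Patients with overt disease carry little information on that question, because both readings are likely to see it. If they form a sizeable part of the diseased group, the pooled AUCs describe a mixed cohort, and the contrast between modalities no longer reflects occult disease.

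The melanoma exemption is a different flaw in the same list. Melanoma itself metastasises, and a deposit from it could be labelled as spread of the study cancer.

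**Working it through.** **1. Text comparison.**

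| Feature | Abstract, sections 2 and 4.3 | Section 3 |
|---|---|---|
| Nodes | clinically localized | N1 and above admitted |
| Distant disease | clinically localized; local treatment considered | no M0 criterion; only treated metastatic disease excluded |
| T threshold | T2 and above (abstract); >T2 (section 2) | T2 (RCC); muscle invasive (bladder) |

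The Introduction sets synchronous metastases at presentation against clinically localized disease at presentation, so the authors' own usage separates the two groups.

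**2. What the documents give on size.** Section 4.4 plans an AUC difference of 0.15, with PET-CT at 0.75 (RCC) and 0.70 (bladder). If PET-CT is the better test, conventional CT is at 0.75 − 0.15 = 0.60 and 0.70 − 0.15 = 0.55. The share of entrants with visible disease, the prevalence and the sensitivities are not given. The Introduction puts synchronous metastases at one third of all RCC cases and metastatic presentation at 5–10% of bladder cases. These are not enrolment shares, but they show that the group need not be negligible.

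**3. Illustration. Every input here is an assumption.**
- A share f enters through CT-visible nodes; 80% of these are truly positive, and study CT reads them all as positive.
- The remaining 1 − f have prevalence 15% and specificity 0.95 for both readings. Sensitivity is 0.30 for CT and 0.60 for PET-CT.
- For a binary reading, AUC = (sensitivity + specificity)/2.

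In the remaining (cN0) patients, CT is (0.30 + 0.95)/2 = 0.625 and PET-CT is (0.60 + 0.95)/2 = 0.775. The difference is 0.15.

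For f = 0.20:
- Diseased: 0.20×0.80 + 0.80×0.15 = 0.16 + 0.12 = 0.28. Non-diseased: 0.72.
- CT sensitivity: (0.16 + 0.12×0.30)/0.28 = 0.196/0.28 = 0.700.
- PET-CT sensitivity, if it also reads the visible nodes as positive: (0.16 + 0.12×0.60)/0.28 = 0.232/0.28 = 0.829.
- Specificity, both: 1 − (0.04 + 0.68×0.05)/0.72 = 1 − 0.074/0.72 = 0.897.
- AUC: CT 0.799, PET-CT 0.863. Difference 0.064.
- If PET-CT instead clears every false-positive node, its specificity is 1 − 0.034/0.72 = 0.953 and its AUC 0.891. Difference 0.092.

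The same steps for other shares:

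| f | Diseased | Overt share of diseased, g | CT AUC | PET-CT AUC (same reading of nodes) | Difference | Difference if PET-CT clears false-positive nodes |
|---|---|---|---|---|---|---|
| 0.10 | 0.08 + 0.135 = 0.215 | 0.372 | 0.743 | 0.837 | 0.094 | 0.107 |
| 0.20 | 0.16 + 0.12 = 0.28 | 0.571 | 0.799 | 0.863 | 0.064 | 0.092 |
| 0.30 | 0.24 + 0.105 = 0.345 | 0.696 | 0.825 | 0.871 | 0.046 | 0.091 |

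**4. Cross-check.** When both readings treat overt patients alike, the difference is (1 − g) × 0.15. For f = 0.20 this is 0.429 × 0.15 = 0.064, which agrees. Milder overt shares of 10%, 25% and 50% of the diseased give 0.135, 0.113 and 0.075.

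**The case against.** Several points on the other side are fair.

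- **Size.** A reader might set the rise in the CT AUC (0.625 to 0.80) against the planned 0.15 and call the distortion as large as the effect. That is the wrong comparison. The planned effect is a difference between modalities, every patient gets both readings, and overt disease lifts both AUCs. What matters is the change in the difference, 0.15 to 0.064 or 0.092 at f = 0.20. The inputs are also strong: at that share, 57% of diseased patients are overt.
- **Positives by selection.** A reader might infer that these entrants are conventional-imaging positives by construction. Section 3 names no entry modality and also accepts biopsy findings. The test under study is a new CECT, read blind to the nuclear medicine report, with equivocal scans counted as negative. Entry findings need not recur as positives.
- **Direction.** Dilution is probable, not certain. Clearing false-positive nodes works in favour of PET-CT, and that gain grows as fewer entry nodes are truly diseased.
- **Bias.** Accuracy in a mixed cohort is not biased for that cohort. Section 3 also states an aim of studying patients at significant risk of metastasis, which fits N1 entry, and the study name in section 2 says high-risk rather than localized. The problem is therefore one of applicability and case mix. The conflict with the abstract and sections 2 and 4.3 remains.
- **M1.** Untreated metastatic disease is admitted by omission and is nowhere named; the words after N1 may mean higher N stages. Section 4.3 states an expectation of local treatment, but it is narrative and not a criterion, so it filters nobody out.
- **T2.** The > sign in section 2 is probably a slip for ≥, since the abstract and the RCC criterion both include T2.
- **Melanoma.** Biopsy is encouraged and surgical pathology is compared with imaging, so misattribution could happen but does not have to.

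**Conclusion.** The point holds as a conflict between the stated population and the entry criteria. N1 entry is explicit; entry of untreated M1 disease follows only from the lack of an M0 criterion. Because nodal and distant metastases are what the primary end point counts, disease already visible at entry raises the apparent sensitivity of both readings and probably shrinks the difference between them.

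The documents do not fix the amount. Under the assumptions above, with 10% to 30% entering through CT-visible nodes, a difference of 0.15 in cN0 patients becomes roughly 0.05 to 0.11 in the pooled cohort; at 20% it is 0.06 to 0.09. The protocol does not say which case mix its planning AUCs describe, so this shows how sensitive the contrast is and does not prove a loss of power. What does follow is that a pooled result cannot be read as an answer for clinically localized disease.

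The melanoma wording is a separate, smaller flaw: cases will be few, but as written they are eligible and could be scored as spread of the study cancer. The T2 wording is a minor correction.

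**What to change.** 1. Reconcile the abstract and sections 2, 3 and 4.3 in one of two ways. Either drop clinically localized from the stated population and objective, or keep it, record cN and cM status on entry imaging, base any claim about localized disease on the cN0 cM0 stratum, and report the node-positive or metastatic stratum separately.
2. Reword the skin-cancer exception to non-melanoma skin cancer.
3. Use one T2 threshold throughout (minor).

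**Cost.** Amended wording and, for the second route, one baseline item. The imaging procedure does not change. The cN0 cM0 estimate rests on fewer patients and has a wider interval, which should be weighed against the planned RCC total of 148 and bladder total of 174.

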## PROCEDURE

4

There will be two subgroups of patients: RCC and urinary bladder carcinoma. In each of these subgroups, the patients will be randomized to either Arm A or Arm B by computer‐generated randomization. In each of the arms, each patient will be subjected to diagnostic imaging by FDG PET‐CT. Patients with elevated alkaline phosphatase or symptoms suggestive of bony involvement will also undergo a bone scan within a week of the PET‐CT scan.

### Acquisition and sequence of FDG PET‐CT scan

4.1

The patients will be kept nil per oral 8 h before the scheduled scan. If any patient will be diabetic, antidiabetic medications will be withheld only on the day of the scan. Blood glucose levels will be measured just before the scan and should be <200 mg/dL. Along with this, the patient's weight and height will be recorded followed by F‐18 FDG administration (0.150.2 mCi/kg body weight) through an 18‐gauge IV catheter. Patients will then be kept in the post injection room and will be ask to take adequate oral fluids for hydration for better background clearance and less radiation retention. Whole body PET‐CECT images will then be acquired from vertex to midthigh in a whole‐body 128 slice GE MIDR PET‐CT scanner, 60–90 min post injection of radiotracer. Scout tomogram will be taken followed by breath‐hold noncontrast scan of thorax, abdomen and pelvis. IV‐iodinated contrast (iohexol—*contrapaque‐300* or iodixanol—*cardiolek‐320*) will be given at the rate of 1.5–2 mL/kg (maximum ~150 mL). For renal mass evaluation, three‐phase images will be acquired in order as follows: cortico‐medullary phase of abdomen–pelvis (~35 s post injection), followed whole body CECT in nephrogenic phase (~70–75 s post injection), whole body PET (12 min/bed, 8–10 beds) and delayed CT of abdomen–pelvis (~15–20 min post injection). Post diuretic dual‐point PET/CT imaging of abdomen will be done ~45–60 min after the whole body PET/CT acquisition. For bladder mass evaluation, two phase image will be acquired as follows: whole body CECT images (venous phase ~60–65 s post injection), followed by whole PET acquisition (1–2 min/bed, 8–10 beds) and delayed CT of abdomen and pelvis (~15–20 min post injection). Interpretation of PET‐CT images will be done by visual and semiquantitative (SUVmax) analysis.

Images of all sequences of the FDG PET‐CT will then be provided in a compact disc (CD) drive for interpretation. A nuclear medicine specialist will review the FDG PET‐CT and provide a detailed written report as per established departmental format for reporting. A radiologist will review the images of the CECT sequences and will provide a detailed report as per established reporting format. Both the reports will be prepared independent of each other, that is, the radiologist will be blinded to the report given by the nuclear medicine specialist and vice versa. Both these reports will then be sequentially reviewed by two clinicians as per the schema described in the following paragraphs.

In Arm A, for each patient, the report of the conventional imaging modality, that is, CECT and bone scan if done, will be first reviewed by the clinicians, and based on this report, a management plan will be made. Then, the PET‐CT report will be reviewed, and change in the management plan if any will be noted. New findings or equivocal findings if any in the PET‐CT report would be noted. In Arm B, the report of the PET‐CT report will be reviewed first by the clinicians, and a management plan will be made. Then, the CECT report and the report of the bone scan if any will be reviewed, and any change in the management plan will be noted.

Positive scans for distant metastases or loco‐regional lymph nodes are to be identified using the following criteria (any one of the following):
Histopathology demonstrating metastatic malignancy.Typical appearance of metastatic disease on scan.Presence of lesion correlating with clinical signs and symptoms.

Confirmation of metastatic lesions demonstrated on scans is strongly encouraged using biopsy or other imaging modalities. However, this is not binding and is left to the discretion of the clinicians. Management impact will be classified as follows:
High impact: Change in management intent or modality.Medium impact: Change in delivery of modality, but not intent.Low impact: Management plan was not altered.Potential impact ignored: Management plan was not altered despite positive findings in the second reviewed report after negative first report.

### Follow‐up imaging

4.2

Follow‐up imaging for those that undergo curative treatment would be done for all patients using the same sequence of FDG PET‐CT at 6, 18, 30, 42 and 54 months. Initiation of any adjuvant or salvage treatment, appearance of local or distant metastatic disease or death of the patient or loss to follow‐up would also be noted.

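### Whether a positive scan is later verified depends on the treatment it triggers, so false positives that divert patients from curative treatment may go undetected and accuracy may be biased

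*Protocol article*

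**What the plan says.** All references are to the protocol article.

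- **Follow-up imaging (4.2).** The scheduled scans are assigned as follows: "Follow‐up imaging for those that undergo curative treatment would be done for all patients using the same sequence of FDG PET‐CT". The sentence names both curatively treated patients and all patients. Its natural reading is all curatively treated patients, but it is ambiguous. Five time points are set, "at 6, 18, 30, 42 and 54 months". The next sentence adds that "appearance of local or distant metastatic disease or death of the patient or loss to follow‐up would also be noted", with no express limit to curative patients.
- **Clinical management (4.3).** "Pathological findings at surgery will be compared with imaging". This can cover only operated patients, who are expected to be the majority; no figure is given.
- **Acquisition and sequence of the scan (4.1).** A scan is positive if any one of three criteria is met, and one of them is "Typical appearance of metastatic disease on scan". On verification: "Confirmation of metastatic lesions demonstrated on scans is strongly encouraged using biopsy or other imaging modalities". The article then qualifies this: "However, this is not binding and is left to the discretion of the clinicians". The top management-impact category is "High impact: Change in management intent or modality".
- **Endpoints (listed after 4.4).** The primary endpoint is the AUC of PET-CT against that of conventional imaging. Incremental accuracy counts patients upstaged from M0 to M1 by the second report. Follow-up is used for the prognostic value of a negative baseline PET-CT and is not named as a reference standard for the baseline scans.

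**The concern.** An accuracy estimate needs true disease status for scan-positive and scan-negative patients alike. Here the index report helps decide who will have later evidence. A patient judged free of metastasis usually proceeds to curative treatment, which brings up to five scheduled scans and, if there is surgery, pathology. A patient whom a positive report moves to non-curative treatment has neither, and any confirmation is optional. Missed disease therefore has planned routes to discovery, while a false alarm that changes treatment has only a discretionary one.

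Three results are exposed: the primary AUC comparison, the count of upstaged patients, and the trial's third hypothesis, which attributes management impact to improved accuracy. Changes from curative to non-curative intent are the ones with the least assured verification.

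**Working it through.** **The text.** For a patient moved off curative treatment by a positive report:

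| Source of verification | Curatively treated | Moved off curative treatment |
|---|---|---|
| Scheduled imaging (4.2) | yes, five time points | none, on the natural reading |
| Surgical pathology (4.3) | if operated | none |
| Biopsy or other imaging of a positive lesion (4.1) | encouraged | encouraged, not required |
| Noting of disease appearance, death, loss (4.2) | yes | not excluded |

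The last row gives little help: noting that disease appears does not settle whether a lesion already called metastatic was so at baseline.

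**Possible size.** The plan gives no figure for prevalence, sensitivity, specificity or the share verified, so there is no verification figure to reproduce. From the plan I take the RCC sample size (134 × 1.10 = 147.4, rounded up to 148) and the planned AUC difference of 0.15. Assumed: prevalence 25%, sensitivity (Se) 0.75, specificity (Sp) 0.90, 60% of positives switched, none of these confirmed. For a binary test, AUC = (Se + Sp)/2.

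- Diseased: 148 × 0.25 = 37. Non-diseased: 111.
- True positives: 37 × 0.75 = 27.75. False positives: 111 × 0.10 = 11.10. True negatives: 99.90.
- Switched and unverified: 0.6 × 27.75 = 16.65 true and 0.6 × 11.10 = 6.66 false positives; total 23.31.
- True AUC: (0.75 + 0.90)/2 = 0.825.
- Unverified dropped: Se = 11.10/20.35 = 0.545; Sp = 99.90/104.34 = 0.957; AUC = 0.751.
- Unverified taken as called: Se = (27.75 + 6.66)/(37 + 6.66) = 34.41/43.66 = 0.788; Sp = 0.957; AUC = 0.873.

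The same formulas with other switch rates:

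| Switched | Unverified | AUC if dropped | AUC if as called |
|---|---|---|---|
| 40% | 15.5 | (0.643 + 0.938)/2 = 0.79 | (0.777 + 0.938)/2 = 0.86 |
| 60% | 23.3 | 0.75 | 0.87 |
| 80% | 31.1 | (0.375 + 0.978)/2 = 0.68 | (0.798 + 0.978)/2 = 0.89 |

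**Partial confirmation.** Take Se = Sp = 0.75 instead, which gives AUC 0.75, the plan's RCC assumption, with prevalence 20% and unconfirmed false positives counted as disease. Then there are 29.6 diseased, 22.2 true positives, 29.6 false positives and 88.8 true negatives. If half the false positives are confirmed as false, 14.8 are counted as disease: Se = 37.0/44.4 = 0.833, Sp = 88.8/103.6 = 0.857, AUC = 0.845. At 75% confirmed the AUC is 0.80; at 100% it is the true 0.75. With half confirmed, the shift over prevalence 30% to 10% is about 0.08 to 0.12.

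**The difference between tests.** Return to the first example, with the 60% switched on PET-CT calls and taken as called. Give CECT an assumed Se of 0.60 and Sp of 0.90: 22.2 true positives, AUC 0.75, true difference 0.825 − 0.75 = 0.075.

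- CECT negative in all 6.66 false positives: Se = 22.2/43.66 = 0.508; Sp = 93.24/104.34 = 0.894; AUC 0.701. The difference reads 0.873 − 0.701 = 0.172.
- CECT positive in all 6.66: Se = 28.86/43.66 = 0.661; Sp = 0.957; AUC 0.809. The difference reads 0.064.

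The bias in the comparison therefore turns on discordant calls.

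**The case against.** The strongest reply is that the defect lies elsewhere. Follow-up imaging serves the prognostic endpoint, recurrence after definitive therapy, and for that purpose restricting it to curatively treated patients is sensible. The weakness is the rule in 4.1 that scan appearance alone can make a scan positive. Had confirmation been required at baseline, these patients would have had reference data before any switch. That stands: this point is largely a consequence of the baseline rule and does not replace correcting it. But with confirmation optional, as written, no planned data collection fills the gap later.

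A reader might also infer several stronger claims that the text does not support.

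- *Diverted patients are never checked and false positives cannot be found.* Biopsy or other imaging is strongly encouraged, and histopathology is one of the positivity criteria. The text supports an unknown share confirmed, not zero.
- *Follow-up stops.* Only scheduled imaging is tied to curative treatment; the noting of disease, death and loss is not so limited.
- *All high-impact changes go unverified.* A change of modality can remain curative and keep its scheduled scans. Equally, not every scan-negative patient is certain to be operated.
- *Accuracy is always inflated, and the test that switches more patients gains most.* The AUC falls if unverified patients are dropped and rises if they are taken as called. Both reports exist for every patient, so the effect on the difference depends on discordance.

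An article condenses its protocol, but the non-binding confirmation and the tie to curative treatment are stated text, not omissions.

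**Conclusion.** The point holds in limited form. Verification depends on the result under test, through the treatment that the result prompts. An unknown share of false positives may go undetected, and sensitivity, specificity and AUC may be biased in either direction. With 60% of positives switched and none confirmed, the handling of about 23 patients alone moves the binary-test AUC between 0.75 and 0.87. That spread of 0.12 compares with a planned difference of 0.15. Prevalence, accuracy and switch rate are assumptions without a source in the article, and no confirmation is the extreme case; any discretionary confirmation shrinks the effect. The figures show that the problem can matter for the primary endpoint; they do not predict its size. The sample-size figures neither support nor weaken the point.

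**What to change.** 1. **Section 4.2.** Resolve whether scheduled imaging applies to curatively treated patients or to all patients. State that outcome data (routine-care imaging, any biopsy, progression and vital status) are abstracted for every randomised patient whatever the treatment, with no study-mandated scan or biopsy.
2. **Endpoint definitions.** Report accuracy, upstaging and high-impact changes by verification status. Add a sensitivity analysis of the PET-CT minus CECT AUC difference that takes the unverified positives as all true and then as all false.

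The cost is a short amendment, some chart abstraction at one centre and one further analysis; clinical management is untouched. Abstraction is best done prospectively, since later records may be incomplete. Routine imaging is less uniform than study scans, and how a lesion behaves under systemic treatment is imperfect evidence of metastasis at baseline, so some patients will stay unverified; the bounds are there for them. This complements correction of the scan-appearance rule in 4.1.
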